## Methods

### Study design and setting

A randomized controlled trial (RCT) parallel groups waiting list design with three measurement points will be used to assess the efficacy of an Internet-based stress recovery intervention FOREST for HCWs, i.e., nurses (superiority trial). We aim to recruit 600 participants in Lithuania and, based on previous e-health studies [17], we expect a dropout of 30%. This will generate sufficient statistical power to detect differences between the groups on the primary outcome measure of stress recovery given a significance level of .05 and a power of 80% [18]. Participants will be randomly allocated to the intervention or a waiting list control group with an allocation ratio of 1:1. Participants allocated to the intervention condition will receive the intervention immediately after randomization, and participants in the waiting list condition will be offered the same intervention 6 months later. The intervention will last for 6 weeks. The pre-test, the post-test, and the 3-month follow-up will be carried out at the same time in both study groups. We will compare stress recovery, PTSD and CPTSD symptoms, moral injury, perceived stress, anxiety, depression, and psychological well-being in nurses who participate in the FOREST intervention vs. those on the waiting list. All study measures will be self-reported and administrated via a secure web application [19]. All participants included in the study will get personalized login data on the first day of using the program. Once participants of the study create a secure password, they will be able to log into the platform where they will have access to the content of the intervention, as well as communication with a psychologist. All the content on the platform is private and protected by end-to-end encryption and participants use secure login for each connection to the platform.

This study protocol is following the Standard Protocol Items: Recommendations for Interventional Trials (SPIRIT) 2013 Checklist [20]. The information regarding enrolment, intervention, and assessments in the trial are presented in Table 1. In addition, the details of the rationale of the study are shown in the flowchart (Fig. 1). The ethics approval for the trial was obtained from the Institutional Psychological Research Ethics Committee of Vilnius University (2021-03-22/61). All study participants will be also asked to give a written consent online in order to participate in the study.

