### Data management

Outcome data will be collected at the three time points using the secure online platform [19]. In addition, data on the usability of the program, such as number of logins, completed exercises, or texts to a psychologist, will be collected within the same platform. All participants will be given an anonymous identifying number. Access to data will be restricted to researchers directly involved in the study only and via a secure login with two-step authentication. All data collected will be stored and managed according to current national regulations of personal data management. All participants will be informed that the data provided will be treated confidentially and will be made aware that in published reports it will not be possible to identify any individual or attribute any information to them.

The collected data will be exported and inputted into SPSS files for analyses and saved on secure university storage. The data file with personal information will be accessible for the researchers directly involved in the study only. Access to the data file with an anonymous identifying number may be provided for the senior and/or junior data analyst as well as made publicly available as a part of the open research data policy required by the journal as a condition for publication of research outputs.

Dropout or premature termination from the study at any point after randomization will be recorded. Participants will be able to choose to withdraw from the study at any point and may ask that previously collected data not be used. Unless a participant has withdrawn consent to participation, repeated attempts will be made to contact participants who will not complete the outcome assessments. All participants will be asked to complete the study measures at each point of measurement, regardless of protocol adherence or any previously uncompleted measures.

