### Statistical analyses

As the study aims to capture the possible change in primary and secondary outcomes in the intervention group, in comparison to the control group, a series of mixed multivariate repeated-measures ANOVAs with time (pre-test, post-test, and follow-up) as a within-subject factor and group (intervention vs. control) as a between-subject factor will be performed. Continuous data aggregation will be used; the change from baseline of the outcome measures sum scores will be recorded. Additionally, we will calculate both within- and between-group effect sizes. The between-group effect sizes will be calculated by using the mean difference from pre-test to post-test (for the short-term effect) and from pre-test to follow-up (for the long-term effect) in the intervention and control groups and the standard deviations of each group at the pre-test [32]. The within-group effect sizes will be calculated by using the means in each group at pre- and post-test/follow-up and standard deviations at each measurement point. The magnitude of the effect expressed in *d* will be interpreted as follows: 0.50 = medium effect and ≥ 0.80 = large effect [18]. The data will be analyzed by using the intention-to-treat principle [33]. The missingness of the data will be treated by using the multiple imputation method [34].

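### With 30% dropout expected, a baseline-adjusted REQ difference at each visit would suit multiple imputation better than an omnibus ANOVA test, with a sensitivity analysis for the missing outcomes

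*Protocol article*

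**What the plan says.** Under Statistical analyses, the Protocol article plans "a series of mixed multivariate repeated-measures ANOVAs with time (pre-test, post-test, and follow-up) as a within-subject factor", with group as the between-subject factor. It adds standardized effect sizes for change from pre-test to post-test (short term) and from pre-test to follow-up (long term). The analysis follows intention to treat, and "The missingness of the data will be treated by using the multiple imputation method". A source is cited for the method. The text names no imputation model, pooling rule or missingness assumption.

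Under Study design and setting: "We aim to recruit 600 participants in Lithuania", "with an allocation ratio of 1:1", and "we expect a dropout of 30" per cent. The dropout is not split by arm or by time point.

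Two statements under Data management bear on the point. Outcome measures are sought from everyone at every time point, whether or not they adhere, with repeated contact attempts unless consent is withdrawn. Also, "data on the usability of the program, such as number of logins, completed exercises, or texts to a psychologist, will be collected" on the same platform as the outcomes.

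**The concern.** There are two separate questions.

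The first is fit between test and imputation. Multiple imputation produces several completed datasets. The basic Rubin's rules combine a scalar estimate and its standard error across them. An omnibus group-by-time F is neither, so the analyst must choose a further rule to obtain one primary p-value. Even when pooled, that p-value says only that the arms differ in profile somewhere over three time points. It does not say whether the difference is at post-test, at follow-up or at both, although the plan wants to report these as distinct effects.

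The second is what imputation assumes about the missing. At 30% dropout, about 180 of 600 participants (600 × 0.30) may need imputed outcomes. Imputation by arm under missing at random assumes that a nurse with no outcome improved as much as a nurse in the same arm with similar observed data. If those lost from the intervention arm in fact did worse, the intention-to-treat estimate is too favourable to FOREST.

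**Working it through.** **Inputs from the document.** N = 600, 1:1, 30% dropout, "given a significance level of .05 and a power of 80" per cent; two groups, three times.

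**Assumptions, not in the document.** SD 1; correlation 0.5 between time points; completer effect d = 0.30; equal loss by arm; 30% missing at both post-baseline times; two-sided test. The simulation used 300 per arm, 20 imputations and 1,500 runs per scenario.

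**1. The plan's own figure.** 600 × 0.70 = 420, or 210 per arm. At 80% power the detectable effect is (1.960 + 0.842) × √(2/210) = 0.273. No effect size is stated for the sample size, so 600 can be neither reproduced nor called wrong. The assumed d = 0.30 is close to this value.

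**2. Can the F-test be pooled?** Degrees of freedom: (2 − 1) × (3 − 1) = 2. Pooling with the multivariate extension of Rubin's rules (the D1 Wald-type F), the simulation rejected in 4.2% of runs under no effect (nominal 5%) and in 91.6% at d = 0.30. It can be pooled, and error is controlled.

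**3. What by-arm imputation assumes.** Let p be the share missing in the intervention arm and f the fraction of the completers' gain that the missing really had.
- True effect over all randomized: d × (1 − p(1 − f)).
- Missing-at-random, by-arm estimate: d.
- Relative overstatement: 1/(1 − p(1 − f)) − 1.

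| p | f | Overstatement |
|---|---|---|
| 0.30 | 1 (missingness unrelated to outcome) | 0% |
| 0.30 | 0.5 | 1/0.85 − 1 = 18% |
| 0.30 | 0 (no gain at all) | 1/0.70 − 1 = 43% |
| 0.10 | 0 | 1/0.90 − 1 = 11% |
| 0.40 | 0 | 1/0.60 − 1 = 67% |

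In absolute terms, at p = 0.30 and f = 0 the gap is 0.30 × d: 0.08 at d = 0.273, 0.09 at d = 0.30 and 0.15 at d = 0.50.

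The simulation agrees, with group in the imputation model:
- Missingness unrelated to outcome: estimate 0.301, truth 0.30.
- Missing intervention participants without benefit: estimate 0.302, truth 0.21.

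**4. If group is left out of the imputation model.** Both arms' missing receive the same expected gain, so the contrast shrinks to 0.70 × 0.30 = 0.21. The simulation gave 0.209 against a truth of 0.30. The bias now runs against FOREST.

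**5. Change contrast against baseline-adjusted contrast.** Participants must complete the baseline assessment before randomization, so baseline REQ is available for adjustment. With r = 0.5, 300 randomized and 210 observed per arm:
- Change from baseline: SE = √(2 × [0.75/210 + 0.25/300]) = 0.094.
- Baseline-adjusted: SE = √(2 × 0.75/210) = 0.085.

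Here 0.75 = 1 − r² and 0.25 = (1 − r)². Simulation with a finite number of imputations gave 0.095 and 0.086. The adjusted contrast is about 10% more precise, from the same data.

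**The case against.** The strongest defence has four parts.

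- **Pooling.** A reader might infer that Rubin's rules cannot handle the ANOVA and that the plan therefore yields no single primary result. That is too strong. The 2-df test pools by a multivariate extension, and it can be written as two change contrasts that pool by the basic rules. The planned short-term and long-term mean changes are also poolable quantities. What stands is that the omnibus test needs a further rule and does not separate the two effects.
- **Bias.** A reader might infer that the plan will overstate the effect by 43%. The document gives no imputation model, so neither the presence nor the direction of bias follows from it. The 43% needs by-arm imputation and no gain at all among the missing.
- **Who is imputed.** It is tempting to equate stopping the programme with missing outcomes. Data management says otherwise: outcomes are sought regardless of adherence, so some nurses who stop will contribute observed values. High workload, named in the Discussion as a risk to data collection, can also act in both arms. Still, outcomes are recorded on the platform that delivers the programme, and 30% dropout is expected despite these efforts.
- **Level of detail.** Imputation model, pooling rule and sensitivity analyses are commonly left to a statistical analysis plan, and this is a condensed article. Their absence is not an error, and it cannot be said that usage data will go unused. The point rests on the analysis that the article does fix, for which a better choice is available.

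**Conclusion.** The stated pairing is workable but not the best choice. A baseline-adjusted group difference per visit yields one estimate and standard error at each time point, pools directly and answers the short-term and long-term questions separately. Under an assumed correlation of 0.5 and 30% missing, it is also about 10% more precise than a change contrast.

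The effect of missing data on the estimate is conditional. Under by-arm missing-at-random imputation, the overstatement at 30% loss runs from 0% to about 43%, depending on how the missing really fared; omitting group from the imputation model would bias the effect toward zero. The document does not show which of these will occur. Because the answer turns on an assumption that observed data cannot test, for close to a third of participants, a sensitivity analysis is worth having.

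**What to change.** 1. Make the primary analysis a baseline-adjusted group difference in REQ at post-test and at follow-up, from regression or a mixed model for repeated measures, pooled by Rubin's rules. Say how the .05 level applies to the two contrasts, since they replace a single test.
2. Impute separately by arm, using baseline and all available outcome scores. In the intervention arm add log-ins and completed exercises as auxiliary variables. State the missing-at-random assumption.
3. Report a reference-based or delta-adjusted imputation of REQ as a sensitivity analysis. It shows how far the result depends on the assumption about the missing; it need not be a hurdle that the efficacy claim must clear.

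Cost: a little more analysis work. The outcome and usage data are already to be collected, so nothing changes for participants. The sensitivity estimate may be less favourable than the primary one.

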## Discussion

This study will be among the first which will evaluate the effects of the Internet-based psychosocial intervention on stress levels and mental health of nurses in the context of the COVID-19 pandemic. Work overloads and long working hours contribute to high levels of stress in nurses [3] and new solutions are needed for psychosocial care. Nurses are particularly burdened and are at risk for burnout [5]; thus, the study is targeted to nurses.

The current intervention is developed to address the needs of the HCWs by using digital technologies which increases the usability of the program by providing flexibility while accessing the intervention. Access to intervention via their digital device reduces barriers of help-seeking, as participants of the trial can access the program with high flexibility without the need for appointments with mental health professionals which is particularly important for healthcare staff who often have long working hours and busy schedules. Media resources developed for this intervention, such as audio and video recordings, will make the intervention usable and attractive for the users.

The current study will contribute to the development of mental healthcare programs for HCWs. Based on the outcomes of the study, the FOREST intervention can be further developed or offered to the healthcare staff as a tool to cope with work-related stress and increase well-being if outcomes will show positive effects of the intervention on the study participants. Specifically, the study will fill the gap in the scientific knowledge regarding the short- and long-term effects of Internet-based stress recovery intervention on the mental health of HCWs. Additionally, the study will provide evidence of the impact of Internet-based stress recovery intervention on a moral injury which is an especially relevant experience for HCWs [10].

The study contains several potential risks. The target group of the study has high working loads during the COVID-19 pandemic, thus, leading to potential issues in terms of the study participants’ recruitment, data collection, and adherence. Data collection and compliance with study procedure risks will be managed via communication with a psychologist on the platform, periodic reminders to enter the new intervention session, and phone calls aimed to receive feedback about the study.

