The current study aims to test the efficacy of stress recovery intervention FOREST among HCWs, in particular, nurses with high levels of stress in the context of the COVID-19 pandemic. The FOREST intervention was developed based on the theoretical framework of stress recovery [16] which emphasizes the importance of stress self-awareness, life-work balance, and self-care. The program was specifically developed to address the needs of HCWs amid the COVID-19 pandemic and was designed as a CBT and mindfulness-based Internet-delivered intervention to reduce barriers to accessing the intervention.

The primary objective of the trial is:
To evaluate the efficacy of the Internet-based for stress recovery (FOREST) intervention in improving stress recovery among nurses in comparison to a waiting list control group in the context of the COVID-19 pandemic

The secondary objectives are:
2.To assess the effect of the FOREST intervention on posttraumatic stress disorder (PTSD) as well as complex posttraumatic stress disorder (CPTSD) symptoms3.To investigate the effect of the FOREST intervention on moral injury4.To evaluate the effect of the FOREST program on the perceived level of stress5.To assess the effect of the FOREST program on depression and anxiety6.To evaluate the effect of the FOREST program on psychological well-being

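### The plan names one primary outcome (REQ total) but not the ANOVA effect or time point that decides efficacy, so the stated 5% level and 80% power belong to no particular test

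*Protocol article*

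**What the plan says.** Several parts of the protocol article are clear. The primary objective, in Background, is to evaluate the programme "in improving stress recovery among nurses in comparison to a waiting list control group". Under Primary outcome, one instrument is named, the REQ, with a total score from 16 to 80. Under Study design and setting, the level and power are tied to that outcome: "on the primary outcome measure of stress recovery given a significance level of .05 and a power of 80" per cent. All other measures are labelled secondary.

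Other parts are open. The Statistical analyses section specifies a series of mixed repeated-measures ANOVAs, with time (three visits) within subjects and group between subjects. It adds between-group effect sizes for the change "from pre-test to post-test (for the short-term effect) and from pre-test to follow-up (for the long-term effect"). It does not say which ANOVA effect answers the primary objective, or which of the two post-baseline visits does. Neither the objective nor the outcome definition gives a time point.

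The Discussion says the programme can be developed further or offered to healthcare staff "if outcomes will show positive effects of the intervention on the study participants", without saying which outcomes.

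**The concern.** A two-group, three-visit ANOVA gives two tests that compare the arms, and they answer different questions. The group main effect averages over all visits, including the pre-test, where randomised arms should not differ. The group-by-time interaction asks whether the two arms change differently at either later visit. The time main effect does not compare the arms and is not counted here. The short-term and long-term effects then offer two further ways to state the result.

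If the deciding result is not fixed beforehand, it can be chosen after the data are seen, and the stated level no longer describes the efficacy claim. The power statement is affected too: 80% power is a property of a specific test, and the candidate tests have clearly different power at the same true effect.

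**Working it through.** **Inputs from Study design and setting**
- Sample size: "We aim to recruit 600 participants in Lithuania".
- Dropout: "we expect a dropout of 30" per cent.
- Allocation 1:1, level 0.05, power 80%.

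**Assumptions of this check**
- Two-sided testing (sidedness is not stated).
- Equal variances and equal correlation r = 0.5 between visits.

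**1. The plan's own figure.** The article gives no effect size or SD, so 600 cannot be reproduced. It can only be solved backwards.
- Evaluable: 600 × 0.70 = 420, or 210 per arm.
- Detectable standardised difference for a simple comparison of two means: d = (1.960 + 0.842) × √(2/210) = 0.273.
- In the other direction, d = 0.273 needs 211 per arm, 422 in all, and 422/0.70 = 603.

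So 600 is consistent with one comparison at one visit, but the text does not say which.

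**2. Null error rate on REQ when more than one result may count**
- *Group effect or interaction.* With equal correlations the two are independent in large samples, so 1 − 0.95² = 9.75%. Simulation gives 9.7%.
- *Change to post-test or change to follow-up.* Each difference in change has variance proportional to 2(1 − r), and their covariance is proportional to (1 − r). Their correlation is therefore 0.5 whatever r is. The bivariate normal probability that at least one exceeds 1.96 in absolute value is 9.1%.
- *Any of the four.* By simulation, about 14%.
- *Benefit only, either time point.* About 4.5%, against 2.5% for one test.
- *Interaction first, time-point contrasts only if it is significant.* About 4.1%.

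Repeating the simulation at r = 0.7 leaves these rates essentially unchanged. In large samples they do not depend on the sample size.

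**3. Power depends on which test is meant.** Take an assumed true d of 0.25 at both later visits, r = 0.5 and 210 per arm, so √(210/2) = 10.25.
- *Baseline-adjusted difference at post-test:* 0.25 × 10.25/√(1 − 0.5²) = 2.96. Power = Φ(2.96 − 1.96) = 84%.
- *Interaction (2 df):* noncentrality = 105 × 2 × 0.25²/[3 × (1 − 0.5)] = 8.75. Power = 76%.
- *Unadjusted change to post-test:* 0.25 × 10.25/√[2 × (1 − 0.5)] = 2.56. Power = Φ(0.60) = 73%.
- *Group main effect:* the average effect over three visits is 2 × 0.25/3 = 0.167, and the SD of a three-visit mean is √[(1 + 2 × 0.5)/3] = 0.816. Then 0.167/0.816 × 10.25 = 2.09, and power = Φ(0.13) = 55%.

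The same data can therefore have from 55% to 84% power, depending on the test the reader assumes.

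**The case against.** The strongest reply has four parts.

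- *The hierarchy is stated.* There is one primary objective and one primary outcome, and the level is tied to it. This is correct. A reader might infer from the Discussion sentence that any of seven measures could carry the conclusion at 5% each, which would give 1 − 0.95⁷ = 30% if they were independent. The document does not support that. The other measures are secondary, and no level is stated for them. Their multiplicity rule may properly sit in an analysis plan that is not shown. The Discussion sentence is a general remark that asks for positive effects, not a success rule, whereas the 30% also counts significant harm.
- *The stated purpose is to capture change relative to control, which points to the interaction.* This has force, and the group main effect is the less natural choice. But the section does not say so, and a two-degree-of-freedom interaction still leaves open which visit the claim is about.
- *The short-term and long-term quantities are effect sizes, not tests.* This is also correct. The 9.1% and 14% figures apply only if those contrasts are used to support efficacy. If they follow a significant interaction, the error rate stays below 5%.
- *The analysis plan may settle it.* It may. But the deciding effect and visit are part of the primary question, and the published power statement depends on them. The article sets out a model with several possible answers, which goes beyond leaving detail for later.

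**Conclusion.** The point holds for the primary outcome. REQ is the sole primary measure, but no effect or visit is named as decisive, so the 5% and 80% cannot be matched to a test. If either ANOVA effect, or either visit, may establish efficacy, the two-sided error is about 9-10%, and about 14% if any of the four may. Counting benefit only, two visits give about 4.5% instead of 2.5%. These figures assume equal visit correlations of 0.5, 210 evaluable per arm and two-sided tests. They describe what the wording permits, not what the investigators have said they will do.

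No claim is made that error is inflated across the secondary outcomes. The defect is moderate and simple to correct, and it should be corrected before the outcome data are analysed.

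**What to change.** In Statistical analyses, name one primary test. One suitable choice is the between-group difference in REQ total at post-test, adjusted for baseline REQ, two-sided at 0.05. Test the 3-month follow-up in the same way only if the post-test result is significant. This fixed sequence holds the REQ claim at 5%. On the assumptions above it also has more power than the interaction test (84% against 76%). Keeping the ANOVA and naming the interaction as the deciding test, with the time-point contrasts only after it is significant, would also remove the ambiguity.

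Describe the other measures as secondary and supportive. In Study design and setting, attach the power statement to the named test. In the Discussion, reword the sentence on offering the programme so that it rests on the primary REQ result.

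This takes a few sentences and no extra participants or procedures. The price is that one time point ranks second: follow-up can be confirmatory only if the post-test result is significant.
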